#### 4.7. Analysis plan.

The analysis plan will include the following:

1. Baseline data analysis will be conducted in order to compare the distribution of sociodemographic and clinical characteristics of participants to test for homogeneity of groups with randomization.
2. Consider compliance with the rehabilitation study protocol at each center and in both arms,
3. Describe and compare participant adherence to the interventions (including voice calls),
4. Consider loss to follow-up to evaluate presence of bias, and eventually adjust in effectiveness analysis
5. An interim analysis for primary outcome in order to assess whether the trial is unlikely to show non-inferiority at the final analysis will be performed when 50% of the sample has been recruited and followed-up 1 year (46).
6. To test the primary hypothesis, recurrent cardiovascular events, differences in proportions will be estimated in absolute and relative ways as absolute risk difference (ARD) and relative risk (RR), respectively. Additionally, a survival analysis will be performed to estimate hazard ratio (HR).
  - a. Both, intention to treat (ITT) and per protocol (PP) analysis will be considered since the ITT makes easier to established the non-inferiority and the PP is considered a more conservative approach. Non-inferiority will be considered established if both ITT and PP analyses support it (31).
  - b. Analyses will be adjusted if unbalances in baseline characteristics are found
7. Depending on the results, subgroup analysis (e.g., sex) may be conducted to explain unexpected differences in outcomes
8. To test the secondary outcomes: For categorical outcomes both, ARD and RR will be estimated. For continuous outcomes, mean differences will be calculated.

[figure not shown]

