### Secondary goals:

- To compare the effectiveness of the abbreviated cardiac rehabilitation programs with the standard program in terms of:
  - o cardiovascular risk factor control (dyslipidemia, hyperglycemia, hypertension, obesity)
  - o exercise capacity
  - o adherence to physical activity recommendations
  - o adherence to diet recommendations
  - o health-related quality of life
  - o exercise related adverse events

**Methodology:** A non-inferiority, pragmatic, multicenter, parallel, single blinded, randomized clinical trial will be conducted. 314 patients with coronary artery disease including Acute Coronary Syndrome (Unstable Angina, Myocardial infarction with or without ST elevation) or stable coronary vessel disease diagnosed by coronariography or stress test, who have received medical treatment, thrombolysis, angioplasty or revascularization surgery will be recruited consecutively, with written informed consent. Participants will be assigned to experimental or standard rehabilitation programs using a permuted blocked randomization scheme. Concealment of assignment will be preserved. The experimental cardiac rehabilitation program includes medical evaluations, 10 face-to-face exercise sessions, diet and smoking counseling, and distance monitoring with text messages and phone calls, delivered by a physiotherapist. The standard cardiac rehabilitation consists of medical evaluation, 20-24 face-to-face exercise sessions, as well as education sessions about diet and smoking, delivered by a nurse, nutritionist and physiotherapist. The main outcome is a composite of cardiovascular mortality and hospitalizations due to cardiovascular causes (non-fatal stroke, non-fatal myocardial infarction, heart failure, and need of revascularization surgery). Secondary outcomes are cardiovascular risk factor control, exercise capacity, adherence to physical activity and diet recommendations, health-related quality of life and exercise-related adverse events. The outcomes will be measured at the end of intervention, at 6 months, and at 12 month follow-up from recruitment. Only main outcome will be a maximum of three year of follow-up. The sample size was calculated considering 5% of non-inferiority limit. Per protocol and intention to treat analysis will be considered. A survival analysis will be run for the primary outcome. One interim analysis is planned when 50% of patients have completed the evaluation at the end of the first year of follow-up.

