#### 4.3. Sample size.

If there is a true difference in favour of the hybrid exercise-based cardiac rehabilitation of 7% in hospitalization rate, then 254 patients are required (127 per group) to be 80% sure that the upper limit of a one-sided 97.5% confidence interval will exclude a difference in favour of the standard exercise-based cardiac rehabilitation group of more than 6%. Considering anticipated loss of follow-up (10%) and the inclusion of an interim analysis that penalizes the power (interim analysis adjustment using Pocock boundary), 314 patients will be recruited (157 per group).

[figure not shown]

This sample size considered the hospitalization and cardiovascular mortality outcomes that was reported in the systematic review by Anderson in 2016 (14), which totaled 18% in the first year of follow-up in those randomized to exercise-based cardiac rehabilitation. The non-inferiority margin was established as is suggested by the Food and Drugs Administration (FDA) (31), which is 50% of the difference between the standard or current therapy (i.e., standard cardiac rehabilitation) and the placebo (or usual care) obtained from a meta-analysis, in this case the same by Anderson (12%).

65

66

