#### 4.6. Outcomes, measures and follow-up.

The **primary outcome** is recurrent cardiovascular events during a minimum of 12 month follow-up. This outcome is a composite of cardiovascular mortality (defined as death by stroke, myocardial infarction or heart failure) and hospitalizations due to a cardiovascular cause (non-fatal stroke, non-fatal myocardial infarction, heart failure, and need for revascularization surgery). Death occurrence will be monitored by study personnel through review of a public registry (Servicio de Registro Civil e Identificación of Chile). The death certificate and any associated medical documentation will be copied for consideration by the adjudicating committee. Hospitalization occurrence will be assessed by study personnel through chart review at each participating center and supplemented by phone calls to participants (in case they received care at another center) every two months, using a standardized script. When the participant reports a hospitalization, all associated documents (i.e., tests and exam reports) will be collected from clinical charts in each center. A central adjudication committee will review all materials. This committee will be composed of three clinician-scientists (at least one will be a cardiology specialist) blinded to participant allocation. Members will make the final decision whether the event is definitive, possible, probable, or if it is rejected, and specify the final hospitalization diagnosis with corresponding ICD-10 code.

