- Adherence: attendance at each supervised session, and also adherence to the calls in the intervention group will be collect.

All outcomes will be measured at the beginning of the program, at the end of intervention (10-12 weeks), at 6 months, and at 12 month of follow-up from recruitment in order to capture acute and long-time impact of interventions. Hospitalizations and cardiovascular mortality will be a minimum of one year and a maximum of three year of follow-up in the cases recruited at the beginning of the study. The personnel assessing outcomes will be blinded to intervention assignment.

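### The 6-point margin stands beside a first-year risk, but the primary comparison is a difference in proportions over an unequal 1 to 3 years with no time point

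*Protocol*

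**What the plan says.** Section 4.3 (Sample size) puts the decision on the absolute scale. The test statistic is the "upper limit of a one-sided 97.5% confidence interval", and the trial is sized so that this bound rules out an excess of more than 6 percentage points in the hybrid arm. The planning assumption is a "true difference in favour of the hybrid exercise-based cardiac rehabilitation of 7% in hospitalization rate". The control risk comes from a meta-analysis, "which totaled 18% in the first year of follow-up in those randomized to exercise-based cardiac rehabilitation". The margin is half of a 12% difference from the same meta-analysis; no time base is written for that 12%.

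Section 4.6 defines the primary outcome as "recurrent cardiovascular events during a minimum of 12 month follow-up". Its closing paragraph gives hospitalizations and cardiovascular deaths "a minimum of one year and a maximum of three year of follow-up", the longest for those recruited first.

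Section 4.7 item 6 tests the primary hypothesis as follows: "differences in proportions will be estimated in absolute and relative ways as absolute risk difference (ARD) and relative risk (RR), respectively". A survival analysis giving a hazard ratio (HR) is additional. Item 6a requires both the intention-to-treat (ITT) and the per-protocol (PP) analysis to support non-inferiority. It names no effect measure and no time point. The Proposal Abstract says: "A survival analysis will be run for the primary outcome".

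**The concern.** A non-inferiority margin has meaning only for a stated effect measure at a stated time. Here the margin is absolute and its companion risk is for year one. The quantity compared with it is a proportion over follow-up that varies between patients from one to three years. As events accumulate, the same relative effect produces a larger absolute gap, so 6 points over the longer period is not the requirement that 6 points at one year would be. The size of the mismatch depends on recruitment speed and on how risk changes after year one, and the plan controls neither.

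The relative risk (RR) and HR are also reported for the primary hypothesis with no margin, and item 6a does not say which measure must support the claim. At stake is whether the trial's main conclusion answers the question its margin was set for.

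**Working it through.** **Inputs from the protocol.** Section 4.3: control risk 18% in year one; planned benefit 7 points, hence 11% in the hybrid arm; margin 6 points; one-sided 2.5%; 80% power; 127 per group evaluable, 157 recruited, 10% loss. Section 4.6: follow-up of 1 to 3 years.

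**Assumptions of this check.** The 12% behind the margin is also a first-year figure (the natural reading). Follow-up is uniform over 1 to 3 years. Hazard is constant, or falls to a half or a quarter after year one. Hazards are proportional between arms. For power, 157 × 0.9 ≈ 141 per arm, with no adjustment of the critical value for the interim look.

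**Step 1: the plan's own figure.** n per group = [0.18×0.82 + 0.11×0.89] × (1.96+0.84)² / (0.06+0.07)² gives 115, so 230 in total. With a continuity correction it is 129, so 258, within 2% of the stated 254. The plain formula gives exactly 127 per group at 20% v 13%, rates the protocol does not state. In each case this is a single-horizon risk-difference calculation with no term for length of follow-up.

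**Step 2: what the margin means at one year.** 18% v 24% has RR 0.24/0.18 = 1.33 and HR ln(0.76)/ln(0.82) = 1.38.

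**Step 3: the same gap over 1 to 3 years.** With λ = −ln(1−p) and hazard fλ after year one, the expected crude risk is 1 − e^(−λ) × [1 − e^(−2fλ)]/(2fλ). Here λ = 0.1985 for 18% and 0.2744 for 24%.

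| Hazard after year one | Control | Arm at the margin | Gap |
|---|---|---|---|
| Unchanged (f = 1) | 32.3% | 41.5% | 9.2 points |
| Half (f = 0.5) | 25.6% | 33.5% | 7.9 points |
| Quarter (f = 0.25) | 21.9% | 29.0% | about 7 points (7.05 before rounding the two risks) |

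**Step 4: what 6 crude points allow.** Solving for the HR that gives a 6-point crude gap: about 1.24 for f = 1 (equivalent to 18% v 21.9% at one year), 1.29 for f = 0.5 and 1.32 for f = 0.25, against 1.38 at one year.

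**Step 5: power at 141 per arm, constant hazard.** Power = Φ[(0.06 + benefit)/SE − 1.96].

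- Arms truly equal, 12 months: SE = √(2×0.18×0.82/141) = 4.6 points; power 26%.
- Arms truly equal, 1 to 3 years: SE = √(2×0.323×0.677/141) = 5.6 points; power 19%.
- Planned 18% v 11%, 12 months: SE 4.2 points; power 88%.
- The same benefit persisting proportionally (HR ln(0.89)/ln(0.82) = 0.59), 1 to 3 years: 32.3% v 20.6%, SE 5.2 points; power 93%.

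**The case against.** **Much of the decision rule is already implied.** Section 4.3 places the confidence limit on the absolute difference, item 6 names proportions first, and RR and HR have no margin to be tested against. Formal naming of the deciding measure is often left to a SAP. This stands: the absolute risk difference is the implied lead, and the open choice of measure is the lesser part of the point. It does not supply a time point, and the protocol's own follow-up text points away from 12 months.

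**The direction is conservative.** Also true. Keeping 6 points over longer follow-up is stricter in relative terms, so the mismatch in horizon does not by itself make a false non-inferiority claim easier.

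**The size rests on assumptions.** True: the 9.2-point figure needs a constant hazard, which no document supports, and the mismatch shrinks to about one point if later risk falls to a quarter.

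Three stronger readings are tempting but unsupported:

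- *Patients lost to follow-up are counted as event-free.* No text says so. Section 4.7 item 4 foresees considering loss to follow-up and possibly adjusting for it. Section 4.6 finds deaths in a public registry and hospitalizations by chart review and two-monthly calls.
- *The abstract contradicts 4.7.* It says a survival analysis will be run, and 4.7 does run one. It does not call it the deciding analysis.
- *The longer window costs power.* Only if the arms are truly equal. Under the benefit the trial was planned on, power rises.

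**Conclusion.** The point holds as a mismatch between margin and test, and it should be fixed. The protocol fixes a 6-point absolute margin beside a first-year risk and applies it to proportions accrued over an unequal 1 to 3 years. Given follow-up uniform over that range, a one-year gap equal to the margin would show as roughly 7 to 9 points, depending on how far the hazard falls after year one. Six points over the longer period tolerates a smaller relative excess: HR about 1.24 to 1.32 across those hazard patterns, instead of 1.38. The effect on power has no single direction: 26% to 19% under equality, 88% to 93% under the planned benefit if it persists proportionally. That the 12% behind the margin is a first-year figure is inferred, not written. The abstract's 5% limit is a separate discrepancy; 6 points is used here because Section 4.3 derives it and sizes the trial on it.

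**What to change.** In Section 4.7 item 6, state that non-inferiority is decided by the upper one-sided confidence limit of the difference in 12-month cumulative incidence of the primary outcome from randomization (Kaplan-Meier, censoring at loss to follow-up), compared with the margin in both the ITT and the PP analysis. State that RR, HR and the 1-to-3-year results are supportive and play no part in the claim. In Section 4.3, write the time base of the 12% difference.

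The cost is wording only. Every patient is planned to have at least one year of follow-up, so no data collection changes. The downside is that events after 12 months no longer enter the decision. If the sponsor wants them to count, a primary HR would be equally coherent, but it would need its own pre-specified margin and a re-derived sample size.

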#### 4.8. Quality control

All processes involved in the study will be overseen. Specific actions are the following:

- Central management office: a central coordination center will be established, responsible for all general processes in the study such as securing and managing ethical and regulatory approvals, document and questionnaire preparation, field personnel training, measurement standardization, and data entry monitoring. The central coordinator will be responsible maintain regular communication with participating centers, solve problems and supervise the overall integrity of the study.
- Center coordinators: each center will have a local coordinator in charge of trial activities such as recruitment, random assignment, coordination of assessments, and sending data to the central office. The critical issues for which the coordinator is responsible include ensuring assignment concealment and blinding of outcome assessments.
- Monitoring: a professional with documented training in Good Clinical Practice (GCP) (47) will be engaged in order to monitor the conduct of the trial. The purpose will be to verify:
  - The protections of the rights and well-being of participants.
  - That the data obtained will be accurate, complete and checked against source documents.
  - That the study is consistent with the approved protocol, and is undertaken in accordance to the GCP guidelines and ethical requirements.

#### 5.0 Ethical Issues

A number of treaties and declarations have been published, which outline the fundamental principles of ethical conduct in biomedical research. In the design of this proposal, the fulfillment of ethical principles of the Belmont Inform has been considered: the value of the research question, methodological rigor, investigators are scientifically-qualified, independent protocol evaluation, and plan that results will be published in a punctual and precise way. The specific bioethical values to be considered are:

- Respect for autonomy: all participants will decide freely on their enrolment after being given sufficient information and time to understand the information about the study; this will be demonstrated through signing an inform consent form.
- Beneficence: benefits and knowledge that will be gained has been considered, and is expected to be bigger than risks or discomforts. Additionally, considering the proven effectiveness of the standard exercise-based cardiac rehabilitation, the actual situation of exercise-based cardiac rehabilitation delivery in Chile, and the recent recommendations for an adapted model of cardiac rehabilitation for low-resources settings, the research design proposed is highly appropriate; indeed, the decision to use a non-inferiority active control study design instead of a superiority design is an ethical one. Specifically, this design is chosen when it would not be ethical to use a placebo, or a no-treatment control, because there is an effective treatment that provides an important benefit available to patients for the condition to be studied in the trial. In this manner, this non-inferiority trial represents a methodological contribution to reduce the exposure of patients only to usual care (48). More specifically, important aspects have been considered in this proposal (49):
  - Definition of non-Inferiority margin, based in the FDA recommendation.
  - Per protocol and intention to treat analysis.
  - Interim analysis.
  - Sample size adjustment.
- Not maleficence: in order to guarantee the participants protection, security and welfare, a research team and collaborators have been assembled to ensure the best quality trial from a clinical and methodological perspective.
- Justice: Participants' selection and recruitment will be performed in a non-discriminatory way, and based on eligibility criteria directly related to the study question. The randomization will guarantee that each participant will have the same probability of being assigned to one or the other group.

The study protocol and the Informed Consent form will be submitted to the corresponding Ethical Committees at the Sponsor Institution and each center where participants will be recruited. At the same time, the protocol will be registered in ClinicalTrials.gov.

[figure not shown]

90

## 6.0 Work Plan:

In the following diagram, a flowchart of the study with activities and the timeline expected is presented.

[figure not shown]

91

92

93

[figure not shown]

94

## 7.0 Work in progress:

**7.1 Economical evaluation in Cardiac Rehabilitation:** A cost-effectiveness study was performed (FONIS SA14ID0005) which evaluated three models of exercise-based cardiac rehabilitation through a Markov Model, concluding that cardiac rehabilitation is highly cost-effective for the public health system in Chile. The analysis of standard cardiac rehabilitation (as will be delivered in the control group in the current study) vs usual care showed an ICER of US\$722.34, and when evaluated the Low-Resource Model of cardiac rehabilitation (service delivered as is recommended by ICCPR Consensus Statement, which is the intervention in the experimental group in this proposal) vs usual care the ICER was US\$665.79. Is important to clarify that there was uncertainty in the estimation of this last model, arising from the fact that the effectiveness was not documented by clinical studies; this is an important justification for the present proposal.

**7.2 Measurements standardization and training:** Procedures to undertake the measurements included in this proposal have been locally standardized and validated. These procedures have now also been applied in other prospective studies (PURE and CESCAS). Investigators from this proposal have adapted, validated or/and developed the operating manuals for: event adjudication, physical measurements (blood pressure, weight, etc) (50,51), 6MWT (52), grip strength (35), IPAQ (38,53), FFQ (43,44), and EQ-5D-3L (FONIS SA14ID0005).

**7.3 International Cooperation:** Contact has been established with ICCPR, and the present chair who lead the development of the low-resource model for cardiac rehabilitation delivery, gave us details of the intervention that were inputs for the economic evaluation described above; she is available for cooperating in conducting this study.

95

96

## 8.0 Available Resources

**8.1 For field work:** We have a scientific team in epidemiologic and clinical studies, that at present is participating in the PURE cohort (3585 participants) and CESCAS cohort (1950 participants). There is also available trained professionals who will deliver the study interventions (physiotherapists), and others who will perform the outcomes measurements in the centers identified (i.e., in each center one coordinator who will be in charge of all processes involved has been identified). The centers have given an anticipate support for conducting the study (upon approval of all regulatory requirements), have capability to implement the interventions, and have cardiac rehabilitation demand that justifies the feasibility of recruitment of the required sample size for the study (around 500 patients per year, and more than 800 in the timeline estimated for recruitment).

The centers are: Complejo Hospitalario San José, Hospital San Juan de Dios, Hospital Regional de Antofagasta, Hospital Clínico de la Universidad de Chile, and Hospital Clínico San Borja Arriarán in Santiago, and Hospital [name] Aravena in Temuco.

**8.2 Research team configuration:** blend seniors with young researchers, and methodological and clinician expertise. We have experience in management of big scale studies, in statistical analyses, database construction, and data entry supervision.

97

98

